### Recruitment {15}

This study will be conducted between the 1st of March 2023 and the 30th of November 2023. This clinical study will be done in a single site, with participants blinded to the treatment assignment. This research is open to patients diagnosed with DED at He Eye Specialist Hospital’s Department of Ophthalmology. Participants will be recruited using adverts in the distribution pamphlets, the website, and social media postings. To ensure efficient recruitment, the study team members will assist in reaching out to potential participants. Additionally, the coordinator of local community centers for old people will be contacted to aid in recruitment efforts. Each participant’s demographic information (including ocular diseases and current/previous usage of drugs and/or lubricating eye drops) will be collected during the first (screening) appointment. Research participants will consist of subjects diagnosed with DM according to the American Diabetes Association’s 2020 “Standards of Medical Care in Diabetes” [28] and dry eye according to diagnostic criteria set by the Asia Dry Eye Society in 2017 [15]. Participants will not be limited based on age, gender, or ethnicity (Fig. 2). Eligible participants will be notified of the study’s procedures and any further arrangements that need to be made. Recruitment will be stopped when the expected number of patients will be recruited in advance.

### Assignment of interventions: allocation

#### Sequence generation {16a}

Patients will be randomized (using a random number table generated by the Microsoft Excel RANDOM function) in a 1:1 ratio after signing the informed consent to the intervention group or control group.

#### Concealment mechanism {16b}

The block size will be concealed from other researchers and the randomization table will not be available for assessment by anyone else involved in the study [29]. Randomization is performed by an independent biostatistician. The biostatistician is the only one who has access to check the file. The allocation list is kept in a separate file on a separate computer under password protection.

#### Implementation {16c}

Opaque and sealed (a randomization list for each stratum) envelopes containing serial numbers will be prepared by an independent statistician and will be delivered to the clinical trial center.

An independent researcher will distribute the envelopes to participants and allocate them into study groups at a 1:1 ratio, without implementing stratification.

Before the random assignment, all participants will be informed that they will be allocated to one of two groups. Random allocation will be conducted at visit 2. Random numbers with corresponding participants will be determined in the order of the time of the second visit and will be opened by the clinician prescribing the eye drops (DQS or HA). The allocation result will not be announced to the participants until the end of the data collection phase of the trial. Researchers collecting and analyzing data related to this trial will be blinded to the participant allocation results.

### Assignment of interventions: blinding

#### Who will be blinded {17a}

The treatment assignment for the study will be triple-masked. Participants in the research would be unable to recognize the contents. The box containing the ampoules is labeled with a batch number, study reference number, participant ID, contact number, investigator name, site address, the expiration date of the eye drops, storage instructions, and a statement informing the participant that the eye drops are for use only in clinical trials and should not be ingested. Masked examiner for all clinical assessments will not involved in the data collection or group allocation procedure for this research. The investigator will not be aware of the two groups.

#### Procedure for unblinding if needed {17b}

There will be no unblinding procedure in this study.

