### Eligibility criteria {10}

Inclusion criteria are as follows:Age ≥18 years(i) A1c≥6.5% (48 mmol/mol); (ii) fasting plasma glucose ≥126 mg/dL (7.0 mmol/L); and (iii) oral glucose tolerance test and random plasma glucose ≥200 mg/dL (11.1 mmol/L)Able and willing to comply with the treatment/follow-up schedule.Bilateral signs and symptoms of DED: (i) Ocular Surface Disease Index (OSDI) questionnaire ≥13, (ii) non-invasive tear breakup time (NITBUT) ≤ 5 seconds, and (iii) conjunctivocorneal staining score (CS) ≥3 points. The presence of two or more criteria was used to establish a positive DE diagnosis, based on the 2017 Asia Dry Eye Society criteria [15].

Exclusion criteria are as follows:Patients with a history of hypersensitivity to any of the ingredients in DQS and artificial tear drops (ATDs).Participants with systemic immune-mediated illnesses, such as secondary Sjögren’s syndrome or graft-versus-host disease.Patients use topical medication(s) for the treatment of ocular disorders such as glaucoma or allergic conjunctivitis.Previous ocular surgery or trauma.1-month history of blepharal and periorbital skin disease or allergies.Severe dry eye with corneal epithelial defect.Limbic keratitis.Pterygium.Corneal neovascularization.Breastfeeding or pregnant women.Rheumatic immune systemic diseases.Herpes zoster infection.Allergic to fluorescein.Contact lens wearers.Patients with active eye infections.Patients with recurrent corneal erosions.Patients with hereditary corneal disease.Patients with punctal plugs or a history of surgical punctal occlusions.

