#### Provisions for post-trial care {30}

There is no anticipated harm and compensation for trial participation but participants who display signs and symptoms of deterioration in their dry eye status will be evaluated by the PI and be directed to their local dry eye center for further evaluation and necessary treatment.

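### The protocol rules out unblinding during the trial with no emergency exception, so a clinician treating a serious suspected reaction has no stated route to the product's identity

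*Protocol article*

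**What the plan says.** Under Procedure for unblinding if needed {17b}, the whole text is: "There will be no unblinding procedure in this study". Four other sections of the protocol article bear on who can learn the product.

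- **Concealment mechanism {16b}**, on the allocation list: "The biostatistician is the only one who has access to check the file".
- **Implementation {16c}**, on participants: "The allocation result will not be announced to the participants until the end of the data collection phase of the trial". The same section says that the random numbers "will be opened by the clinician prescribing the eye drops (DQS or HA").
- **Who will be blinded {17a}** describes triple masking and adds: "The investigator will not be aware of the two groups". The box is "labeled with a batch number, study reference number, participant ID, contact number, investigator name", followed by the site address, expiry date, storage instructions and a trial-use statement. Product name is not among the listed items.
- **Eligibility criteria {10}** exclude "Patients with a history of hypersensitivity to any of the ingredients in DQS and artificial tear drops (ATDs").

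Adverse event reporting and harms {22} provides for stopping treatment promptly and for care by an ophthalmologist when any of five ocular complaints occurs: secretion, irritation, itching, congestion or pain. Criteria for discontinuing or modifying allocated interventions {11b} names the same five. It tells participants to use the *designated* drops and leaves continuation after an adverse event to the principal investigator.

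**The concern.** A masked drug trial normally keeps a narrow way to learn one participant's treatment when care depends on it. Here the heading asks for that procedure and the answer is that there is none. This is a stated rule, so it cannot be put down to a journal article leaving detail to the full protocol.

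What is at stake is care after a serious suspected reaction. The eligibility criteria already treat hypersensitivity to the ingredients of either product as a reason not to give the drops. If such a reaction arises during the trial, what the participant should avoid from then on depends on which product was used. Without a formal route, a worried clinician is likely to ask the prescriber directly. That is a less controlled breach of masking than a code break would be.

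**Working it through.** The point concerns procedure and the plan gives no figure to reproduce. The check compares sections, with two small pieces of arithmetic for scale.

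**1. Who could tell a treating clinician which product was used while data collection is open?**

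| Possible source | What the article says | Stated route? |
|---|---|---|
| Unblinding procedure ({17b}) | None | No |
| Biostatistician ({16b}) | Sole access to the file; no emergency release described | No |
| Participant ({16c}) | Not told until data collection ends | No |
| Investigator ({17a}) | Masked | No |
| Box label ({17a}) | Listed items do not include the product | No |
| Prescribing clinician ({16c}) | Opens the allocation, so may know the product | Informal only |

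**2. Is the code needed for immediate care?** No. Section {22} has the drops stopped and the event treated, and both can be done masked.

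**3. Can it be needed later?** Yes, in a narrow case. After a serious suspected hypersensitivity reaction, which ingredients to avoid depends on the arm.

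**4. How long could the wait be?** Disclosure is tied to the end of data collection for the trial, not to the participant's own last visit. The Trial status section gives recruitment from May to about August 2023. The Recruitment section gives 30 November 2023 as the study end. Assume first entry on 1 May, last entry on 31 August and 56 days of treatment:

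- Last participant's day 56: 31 August + 56 days = 26 October.
- Longest wait, for a reaction on the first participant's first day: 1 May to 26 October = 178 days. If data collection is held open to 30 November, it is 213 days, about seven months.
- Shortest wait, for a reaction at the last participant's last visit: close to zero.

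**5. What would a code break cost in masking?** One participant is 1/202 = 0.5% of the trial, or 1/101 = 1.0% of one arm. This measures the remedy. It says nothing about how often harm would occur.

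**6. The five ocular complaints.** Sections {11b} and {22} list the same five. The first advises use of the *designated* drops, with the principal investigator deciding on continuation. The second stops study treatment promptly. The two fit together if drops are stopped, the event is treated and the principal investigator then decides on resumption. They conflict if *designated* means the assigned study drops. The text does not settle which is meant.

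**The case against.** Much of the case on the other side stands.

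- **Stopping and treating need no code.** This is correct. A reader might infer that participants cannot be treated safely in an emergency, but section {22} does not support that.
- **Only two products are possible, so a clinician can avoid the ingredients of both.** This is workable for a time and narrows the harm. It does, however, set aside hyaluronic acid, which the article calls first-line treatment, for someone who may never have received it.
- **The allocation is disclosed eventually, and someone may already know it.** Both are true. The ban covers the trial period, and the prescriber may hold the answer. It would therefore be too strong to infer that the information is out of reach altogether.
- **Custody and logging rules may sit in the full protocol.** That is fair, and their absence from the article is not the point. The flat statement in {17b} is.
- **Referral after the trial.** Participants whose dry eye worsens "will be evaluated by the PI and be directed to their local dry eye center for further evaluation and necessary treatment". A reader might infer that masking obstructs this care. The provision concerns non-emergency referral, and nothing in the article shows that the local center needs the product name.
- **The two adverse-event sections contradict each other.** A reader might infer this too, but the sequence of stopping, treating and then deciding reconciles them. It is a separate question of wording.
- **The events are described as very rare, and known hypersensitivity is excluded.** Both lower the chance of the scenario. They argue for a procedure that is seldom used, and do not justify having none.

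**Conclusion.** The point holds in limited form and is minor. Section {17b} bars unblinding during the trial without an emergency exception, and no other section supplies a formal route. The consequence is confined to care after a serious suspected reaction, where the wait for the product's identity could run from almost nothing to roughly six or seven months on the assumed dates.

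The rule applies to all 202 participants over 56 days of treatment, but that is its reach and not a count of people harmed. The article gives no rate of serious events, so none is estimated. Sample size and the primary analysis are unaffected.

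The conclusion rests on reading {17b} as written and on treating the prescriber's possible knowledge as informal, because the article gives that clinician no role in disclosure.

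**What to change.** Replace the sentence in {17b} with a single-participant emergency code break:

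- **When:** a serious event in which knowing the product would change care.
- **Who asks:** a treating ophthalmologist who does not assess that participant's outcomes. This must be written down, because at this single site ophthalmologists also carry out the outcome examinations.
- **Who releases:** the biostatistician who holds the list, or a named deputy.
- **Record:** date and reason logged.
- **Afterwards:** outcome assessors and analysts stay masked, and the participant is followed to day 56 and kept in the intention-to-treat analysis.

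As a separate wording change, {11b} should say which drops *designated* means and be aligned with the prompt discontinuation in {22} for the same five complaints. One suitable order is to stop the drops, treat, and then have the masked principal investigator decide on resumption.

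The cost is mainly wording. The list holder exists already, and the contact number on the box could serve as the request point. The downsides are that the list holder or deputy must be reachable, that an occasional participant is unmasked, and that some mild events will interrupt treatment. The amendments section {25} names only eligibility, outcomes and analyses, so it does not expressly cover this change. The revised text should still go to the same ethics committee.

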#### Participant withdrawal

Based on the following criteria, patients will be removed from the research.When it is deemed challenging to continue the study owing to the emergence of new ailments.When the research participant cannot be located.In the case of pregnancy or pregnancy suspicion.When participants want to end their participation in a study.When the participant’s caretaker cannot guarantee their participation in the study.When the research project has concluded.When the lead investigator and sub-investigators believe that it is acceptable to cease the study for reasons other than those listed above.

### Data collection and management

#### Plans for assessment and collection of outcomes {18a}

To prevent data loss, questionnaires will be completed using an online system. Ophthalmic examinations will be performed by experienced ophthalmologists. In order to ensure the accuracy of the results, some tests are averaged three times. Data administration is the responsibility of [name], HESH, Department of Clinical Research, as chosen by the principal investigator ([name]). This research collects data using a proprietary electronic medical records (EMRs) report form and management application, uploaded to the cloud for backup weekly. Following the database lock, the individual responsible for statistical analysis will get the locked data.

#### Plans to promote participant retention and complete follow-up {18b}

To enhance participant adherence, a research assistant will send regular reminders to use the eyedrop and complete the follow-up. If participants discontinue or deviate from intervention protocols, the study team will initiate contact and prioritize addressing any concerns that may be impacting their adherence to the intervention protocols.

In order to guarantee the completeness and accuracy of the gathered data, the online questionnaires will be encoded in a manner that necessitates respondents to provide comprehensive responses to all inquiries prior to submitting their answers. In addition, to increase motivation to remain in the study, participants will receive transportation subsidies after completion of the follow-up

#### Data management {19}

This study uses the electronic case report form and management tool to collect data. Data collection and data entry were performed by separate experienced staff members at HESH, Department of Clinical Research. Participants will not input their names or any identifying information but will be assigned a unique identifier. To ensure data quality, supervision and double confirmation will be performed by [name], along with weekly backup, ensuring that only authorized users (e.g., the research team members) will have access to the dataset.

#### Confidentiality {27}

Participant’s personal information will be kept confidential in the same way as their medical histories in the hospital before, during, and after the trial. During the course of the research, participants’ personal information will be kept strictly confidential and only accessed by authorized persons only. Participants will be allocated an individual trial identification number and participant details will be stored on a secure password-protected database in the clinical trial center. Following the end of the clinical trial, all participant’s data will be anonymized prior to data analysis and will be available from the corresponding author upon reasonable request.

#### Plans for collection, laboratory evaluation, and storage of biological specimens for genetic or molecular analysis in this trial/future use {33}

There will be no biological specimens collected during the entire trial.

### Statistical methods

#### Statistical methods for primary and secondary outcomes {20a}

In this research, unless otherwise mentioned, the significance level is set to 5% two-sided and the confidence coefficient is set to 95%. The demographic data of the study’s subjects will be tabulated by calculating the mean and standard deviation for continuous variables and the frequency and percentage for categorical variables. If the continuous variables do not follow a normal distribution, they will be converted appropriately by logarithmic transformation or other means and aggregated with the mean and standard deviation, or the median and interquartile range will be utilized as descriptive statistics.

The safety analysis will be conducted based on a safety analysis population that includes subjects who have received at least one dose of medication after randomization.

Data will be collected for all patients participating in the treatment at the following stages: baseline, first follow-up at week 4 (day 28), and second follow-up at week 8 (day 56 ). The primary outcome measures for this study are NITBUT scores before and after treatment. For the main endpoint, between-group comparisons using baseline as a covariate and an analysis of covariance will be done to produce the adjusted mean, its 95% confidence interval, and the *p*-value. A paired *t*-test will be used to make within-group comparisons. To ensure participant safety, frequencies and proportions will be computed for each group and item, and comparisons between groups will be made using Fisher’s exact probability test or the *χ*^2^ statistic.

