**Discussion:**

This study will be a standardized, scientific, clinical trial designed to evaluate the therapeutic effects and safety of DQS and HA for diabetic dry eye treatment.

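### Within-arm paired t-tests cannot show that either drop works, because participants are selected for poor values of the outcomes and there is no untreated arm

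*Protocol article*

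**What the plan says.** Statistical methods {20a} sets the general rule that "the significance level is set to 5% two-sided". It describes the primary outcome in before-and-after terms: "The primary outcome measures for this study are NITBUT scores before and after treatment". The two arms are then compared on that outcome with a baseline-adjusted model: "between-group comparisons using baseline as a covariate and an analysis of covariance will be done". The next sentence adds that a paired t-test "will be used to make within-group comparisons". It gives that test no descriptive label and no limit on interpretation.

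Eligibility {10} lists "Ocular Surface Disease Index (OSDI) questionnaire ≥13", "non-invasive tear breakup time (NITBUT) ≤ 5 seconds" and a conjunctivocorneal staining score of at least 3, and then says: "The presence of two or more criteria was used to establish a positive DE diagnosis". All three measures are also outcomes of the trial.

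Trial design {8} and the description of the control arm give two randomised groups, DQS and an active HA control, and no placebo or untreated group. The Discussion paragraph of the abstract calls the trial "designed to evaluate the therapeutic effects and safety of DQS and HA for diabetic dry eye treatment".

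**The concern.** People enrolled because a variable measurement was poor on the day tend to measure better next time, treated or not. Study effects can act in the same direction. Everyone gets daily text reminders and a drop diary (Strategies to improve adherence {11c}) and contact from staff if they deviate (Plans to promote participant retention {18b}). With no untreated arm, nothing in the design separates these from a drug effect. A paired t-test against baseline therefore tests whether the mean changed, not whether the drop changed it.

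What is at stake is a statement that DQS works, that HA works, or that both do. The abstract's wording leaves room for such a statement. So does the non-inferiority framing in Sample size {14}, since two similar arms that each improved significantly are easily reported as two effective treatments.

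**Working it through.** The plan gives no figure for the within-arm tests, so there is none to reproduce. The check asks how often a paired t-test shows a significant improvement in NITBUT when neither drop has any effect.

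**Inputs from the article.** Entry cut 5 s and the two-of-three rule (Eligibility {10}); two-sided 5%, hence 2.5% in the direction of improvement ({20a}); SD 5.23 s and 82 per arm before inflation (Sample size {14}). The SD is a sample-size value, borrowed here for the source population.

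**Assumed.** Source mean 6 to 10 s, test-retest correlation ρ of 0.5 to 0.9, and the qualifying reading used as the baseline.

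**Case 1: everyone selected on NITBUT ≤5 s, normal source, baseline between 0 and 5 s.** Let a = (0 − μ)/σ, c = (5 − μ)/σ, Z = Φ(c) − Φ(a).

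- Truncated mean: e = [φ(a) − φ(c)]/Z
- Truncated variance: v = 1 + [aφ(a) − cφ(c)]/Z − e²
- Expected change with no drug effect: −σ(1 − ρ)e
- SD of change: σ√[(1 − ρ)²v + 1 − ρ²]
- Chance of significant improvement: P(non-central t on 81 df > 1.990), non-centrality = √82 × mean change/SD of change

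Example, μ = 6, ρ = 0.9: a = −1.147, c = −0.191, Z = 0.299, e = −0.620, v = 0.0725. Mean change = 5.23 × 0.1 × 0.620 = 0.32 s. SD = 5.23 × √(0.01 × 0.0725 + 0.19) = 2.28 s. Non-centrality is about 1.29 and the chance of significance 24.5%.

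| Source mean | ρ = 0.5 | ρ = 0.7 | ρ = 0.9 |
|---|---|---|---|
| 6 s | 1.62 s, 89% | 0.97 s, 64% | 0.32 s, 24.5% |
| 8 s | 2.55 s, 99.9% | 1.53 s, 95% | 0.51 s, 51.5% |
| 10 s | 3.48 s, about 100% | 2.09 s, 99.9% | 0.70 s, 78% |

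Without the lower limit at 0, and with source mean 5 to 10 s and SD 2.5 to 5.23 s, the spurious gain is 0.2 to 3.9 s and the rate 37% to nearly 100%.

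**Case 2: the two-of-three rule as written.** Someone with OSDI ≥13 and staining ≥3 enters whatever the NITBUT, which dilutes the effect. The shares meeting the other two criteria are not in the article; 70% for OSDI and 50% for staining are assumed.

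- Lognormal NITBUT (median 6 s, log-SD 0.5), criteria weakly correlated (0.1), 1,000 simulated trials with 91 per arm. For ρ = 0.5, 0.7 and 0.9 (on the log scale), false improvement per arm is 39–41%, 25–26% and 11%. Both arms are significant together in 15%, 7% and 2%. Rerun with 82 per arm, the per-arm rates are 37–38%, 25–26% and 10–11%.
- Normal NITBUT (SD 5.23 s, mean 6 to 10 s, baseline above 0), criteria independent, 82 per arm: 3% to 12% per arm.

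The result is sensitive to the shares. If 90% met each of the other two criteria, these models give 6% per arm or less, in places no more than the nominal 2.5%.

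**Between-arm analysis.** In the lognormal simulation with 91 per arm, under either selection rule, the baseline-adjusted ANCOVA rejected in 4.5% to 5.5% of zero-effect trials, as it should.

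OSDI and staining are exposed to the same mechanism but were not simulated. The reminder and attention effects have no figure.

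**The case against.** The strongest reply is that the inference that matters is already protected. The main endpoint goes to a between-arm ANCOVA adjusted for baseline, the objective is comparative (Objectives {7}), and the paired test is one sentence with no stated role in any conclusion. This stands, and it limits the point to the within-arm tests. A reader might infer that the comparison of DQS with HA is biased; it is not, because randomisation exposes both arms to the same regression. Nor does the article plan to compare the arms by noting significance in one and not the other.

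A reader might also infer that both arms will very probably turn out significant whatever the drugs do. The article does not support that. The high rates need everyone to be selected on NITBUT, while the rule is two of three. Under that rule, in the lognormal model above, both arms are significant together in about 2% to 15% of zero-effect trials.

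Baseline timing matters too. The qualifying examination comes before consent (Informed consent {26a}), there is a first screening appointment (Recruitment {15}), and allocation is at visit 2 (Implementation {16c}). If baseline is re-measured then, much of the regression has already happened. The text does not settle this, and the schedule figure is not available here. Taking the median of three NITBUT readings also reduces noise, which argues for the higher correlations.

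Finally, a within-arm 95% CI carries the same bias as the p-value, so removing the p-value alone changes little. That is correct, and it is why the label and the note matter more than the format.

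What the reply does not remove is that the plan states an inferential test at 5% that cannot answer the question it invites.

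**Conclusion.** The point holds for the within-arm tests only. Selection on the outcomes, two treated arms and an unqualified paired t-test mean that a significant within-arm change is not evidence that the drop works.

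For NITBUT with no drug effect, the rate of false improvement per arm is about 24% to nearly 100% if all enter on NITBUT ≤5 s, and about 3% to 41% under the two-of-three rule with the shares assumed above, against a nominal 2.5%. The 41% is at 91 per arm; at 82 it is about 38%. The rate is lower if baseline is re-measured at visit 2, or if nearly everyone meets the OSDI and staining criteria. Source distribution, correlation and shares are all assumptions, so these ranges show what can happen and do not predict this trial. The conclusion about interpretation needs none of them: it follows from the design.

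**What to change.** In Statistical methods {20a}, remove the paired t-test as an inferential analysis. Report within-arm change as mean and 95% CI, labelled descriptive, with a note that it includes regression to the mean and study effects and is not evidence of drug effect. Add one sentence saying that conclusions about efficacy rest only on the baseline-adjusted DQS minus HA difference. Reword the abstract's Discussion sentence so that the aim is a comparison of the two drops.

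The change is a few sentences of text, with no effect on sample size, data collection or the power of the main analysis. The downside is that within-group p-values are no longer available to report.
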